### Eligibility and recruitment

The target group for the intervention is legal representatives, both professional and volunteer. Additionally, data will be assessed from all people with dementia who are represented by one of the participating legal representatives at least for 2 weeks within the 6-month follow-up (hereby referred to as *persons concerned*).

Legal representatives who represent at least one person with dementia (assessed by the legal representative and / or medical diagnosis) are eligible for inclusion. Exclusion criteria are former participation in the PRODECIDE education program (either the whole program or a single module).

Recruitment will be performed consecutively in cooperation with institutions that offer training for professional or voluntary representatives. Institution cooperation includes recruitment and conducting the education program. Appointments for the education program will be made, and invitations will be published, using the e-mail lists, websites, calendar of events, flyers, etc., of the cooperating institutions. The invitation covers information about both the education program (e.g., target group, content, place and time) and the study (e.g., randomized allocation, offers for the control group).

Potential participants will register at the study center (by phone, e-mail or fax). After screening for eligibility (by phone), the legal representatives will receive information leaflets, the consent form and forms for baseline assessment (by mail or e-mail).

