### Randomization and blinding

After retrieval of written informed consent and baseline data, participants will be allocated to the intervention group or to the control group, stratified by professionals and volunteers (Fig. 1). To ensure a close balance of entities in each group, randomization will be performed by randomly selected block sizes of four and six. The randomization list will be computer generated by a scientist who is not involved in either the intervention or data collection. An independent person will also perform the allocation. As safeguards, no other person will have access to the list, and the list will be sent by e-mail only in an encrypted format.

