### Data analysis

Data will be entered into a SPSS database and double-checked by student assistants blinded to the group allocation. Simple plausibility checks will be done in the study center before the final statistical analysis by the statistician. Analysis of all quantitative data will use the intention-to-treat principle. Missing values in primary and secondary outcomes will be imputed using simple methods. A dropout analysis comparing baseline parameters between the study population and early dropouts (before T2) will be performed.

All statistical tests are two-sided using a significance level of 5%. Baseline parameters are described by frequency tables, means, standard deviations or quartiles.

The primary outcome is the percentage of correct answers for the knowledge test at T1. Assuming approximate normal distribution, the expected values from the IG and CG will be compared with adjustment for stratified randomization by professionals and volunteers using bifactorial analysis of variance (linear model). Distribution assumptions will be investigated by graphical methods. Furthermore, interactions between intervention and professional status will be included in a secondary model. Different effects depending on the professional status will be discussed.

The secondary outcome of sufficient knowledge (binary) at T1 will be compared between IG and CG using bivariate logistic regression, including IG/CG and professional status as independent variables. Additionally interactions between intervention and professional status will be investigated in a second model.

The sustainability of knowledge will be investigated at T3. The time course of the knowledge between T1 and T3 will be analyzed by fitting a linear mixed model: the dependent variable is knowledge (% of correct answers), and the independent variables are IG/CG, time (T1, T3), interaction between intervention and time, professional status and interaction between intervention and professional status. To adjust for repeated measurements of the legal representatives, random effects are included (covariance pattern model with covariance structure compound symmetry).

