Further secondary outcomes are the numbers of persons concerned and the percentage of these persons affected by PEG, FEM or AP (separately) per legal representative at T3. Mean values ± standard deviations will be described for IG and CG at T3 as well as at T0. Linear models will be fitted including IG/CG and initial values at T0 as independent variables.

Finally, the results of the first decision about PEG, FEM or AP by the legal representative after T0 (e.g., after training for IG, or after randomization for CG) will be assessed. Initially, the duration from T0 to the first decision will be described for IG and CG by Kaplan-Meier curves. In case of no decision, durations are censored at the end of observation after 6 months or at dropout. Kaplan-Meier curves between both groups will be compared by the log rank test, as long as there are no clear deviations from the proportional hazard assumption in the graphics. Four categories of decisions will be described by frequency tables.

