### Sample size

No information was available for the primary outcome from previous studies. The assessment instrument was pretested with a before-after design to roughly estimate the expected intervention effect in the primary outcome of knowledge (given as a percentage of correct answers). The knowledge test was revised after three courses with a total of 18 legal representatives. Afterwards, two pilot courses with 16 participants were used to estimate the effect size of the intervention. Fifteen datasets before intervention, and 12 after intervention, were included in the analysis.

A common standard deviation of σ = 0.17 can be assumed in IG and CG. A mean difference of 0.085 between IG and CG can be detected by a power of 90% by the two-sided t-test, using a significance level of 5% based on a sample size of 86 per group (172 overall). Including a maximum dropout rate of 20%, an overall sample size of 216 is planned. The pilot study estimated a larger effect (0.38). Because of the low sample size, and considering a possible bias in the pilot study, the planned sample size is higher than theoretically necessary. It corresponds to a medium effect of 0.5*σ, as suggested by Cohen.

With six to ten participants per training session, the education program will be offered approximately 24 times (12 times per group).

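### The PEG, PR and AP models omit the randomisation stratum and, as written, weight every representative equally: valid, but possibly imprecise

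*Protocol article*

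**What the plan says.** The protocol article's Data analysis section takes, for each legal representative, the percentage of persons concerned who have PEG, physical restraints (written FEM there) or antipsychotics at T3, each measure separately. It then states: "Linear models will be fitted including IG/CG and initial values at T0 as independent variables". No other covariate and no weight is named.

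Two other sections bear on this:

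- Randomization and blinding: "participants will be allocated to the intervention group or to the control group, stratified by professionals and volunteers". In Data analysis this factor enters the primary analysis of variance, the logistic model for sufficient knowledge and the mixed model for T1 to T3.
- Eligibility and recruitment: "Legal representatives who represent at least one person with dementia" may join. The minimum is therefore one person, and no maximum is set.

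**The concern.** With one person, a representative's percentage can only be 0 or 100. With several persons it takes intermediate values and varies less. A plain linear model gives both the same weight and assumes the same residual variance, so the noisiest rows count as much as the most informative ones. The factor used to stratify randomisation is also dropped from these models alone, without a stated reason.

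These outcomes carry the further objective of showing whether training reduces autonomy-restricting measures in people with dementia. No power is stated for them. Avoidable loss of precision makes an uninformative null result more likely.

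**Working it through.** **The plan's own figure.** "A common standard deviation of σ = 0.17 can be assumed in IG and CG", and "A mean difference of 0.085 between IG and CG can be detected by a power of 90% by the two-sided t-test". Normal approximation: n = 2 × (1.960 + 1.282)² × (0.17/0.085)² = 2 × 10.51 × 4 = 84.1, so 85 per group. Noncentral t power is 0.8999 at 85 and 0.903 at 86, so 86 reproduces. Dropout: 86/0.8 = 107.5, so 108 per group and 216 overall, as stated. This covers knowledge only.

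**Inputs.** From the documents: 86 evaluable per group; prevalence 5% (PEG), 12.5% (PR) and almost 30% (AP) in nursing home residents (Background); a minimum of one person per representative. Assumed, because the documents do not give them: the share of representatives with one person (30%, 50% or 60%; 60% is the national volunteer share in Background), m = 2, 5 or 10 persons for the rest, and ICC 0.01 to 0.5.

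**Spread of one representative's percentage.** SD = √[p(1−p)/m] for independent persons. With m = 1 it is 22, 33 and 46 points at 5%, 12.5% and 30%. With m = 8 it is 8, 12 and 16 points.

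**Efficiency.** The variance is p(1−p)·v, with v = ICC + (1−ICC)/m. The relative efficiency (RE) of equal weights against inverse-variance weights is 1/[mean(v) × mean(1/v)].

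Example: half at m = 1 (v = 1), half at m = 5, ICC 0.1 (v = 0.1 + 0.9/5 = 0.28). Mean v = 0.64; mean 1/v = (1 + 3.571)/2 = 2.286; RE = 1/(0.64 × 2.286) = 0.68.

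RE with half the representatives at one person:

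| Persons for the other half | ICC 0.01 | ICC 0.1 | ICC 0.3 | ICC 0.5 |
|---|---|---|---|---|
| 2 | 0.89 | 0.92 | 0.96 | 0.98 |
| 5 | 0.57 | 0.68 | 0.85 | 0.94 |
| 10 | 0.35 | 0.54 | 0.79 | 0.92 |

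Over shares of 30-60% the ranges are 0.89-0.98, 0.57-0.95 and 0.35-0.93.

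**Detectable difference at 80% power**, 86 per group, same example, before T0 adjustment: 2.80 × √[2p(1−p)·v̄/86], where v̄ is 0.64 for equal weights and 1/2.286 = 0.4375 for optimal weights. This gives 0.157 against 0.129 for AP, 0.113 against 0.093 for PR, and 0.074 against 0.062 for PEG. Both PEG values exceed the 5% prevalence, so weighting does not rescue that outcome.

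**Simulation of the stated model** (172 representatives, stratified 1:1, T0 value included, half with one person and half with five, 1,500 runs per scenario):

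- Type I error of the stated model was 3.3-4.9%. A second set with 5 or 8 persons, ICC 0.05-0.10 and all three prevalences gave 3.3-5.3%, with the mean model standard error within about 6% of the empirical one.
- At prevalence 30% and ICC 0.1 under no effect, the empirical standard error was 0.0315 with equal weights and 0.0234 with ICC-based weights. Power for an assumed 30% relative reduction was 73% against 93%. At ICC 0.3 it was 76% against 91%.
- Adding the stratum changed the standard error by at most 0.0001, even with prevalence 20% in the one-person stratum and 40% in the other.
- In that last scenario the estimated effect was −0.090 with equal weights and −0.106 with ICC-based weights, so the choice of weights also changes what is estimated.

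**Crude weights by number of persons.** Same mix, ICC 0.5, so v = 0.6 at m = 5. The variance factor is mean(m²v)/mean(m)² = [(1 + 25 × 0.6)/2]/3² = 8/9 = 0.889, against 0.80 for equal weights: 11% more variance. Over the whole grid, crude weights at ICC 0.5 gave 1-30% more variance than none.

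**The case against.** The strongest case for the plan is that the unit analysed is the unit randomised and trained. Stratified 1:1 allocation balances the unequal variances across arms, and the outcome is explicitly defined per representative. That stands, and it rules out several stronger readings:

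- A reader might infer that standard errors or p-values are wrong because single-person percentages are binary. The simulations show no inflation of type I error.
- A reader might infer that the plan analyses something other than its named outcome. The Outcomes section gives the short name and Data analysis the operational definition. A representative average is a legitimate estimand, and preferring a person average is a choice.
- A reader might take volunteers to have one person and professionals many. The documents set the same minimum for both and give no caseload by status.
- A reader might blame the missing stratum for lost precision. The measured cost is close to nil.

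It can also be said that weights belong in an analysis plan that is not shown. The word unweighted is indeed an inference: the article does not use it. But the article lists the model's terms, and equal weighting is the ordinary reading of a linear model with none named. The omission of professional status is plain on the page, beside three models that include it.

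**Conclusion.** The point holds as a matter of precision and consistency in secondary outcomes. It does not affect validity or the primary analysis. Equal weights are never more precise than optimal ones. How much is lost depends on caseloads and ICC, which the documents do not give: RE is about 0.35-0.98 over the assumed grid and 0.68 in the middle case. The loss is small if numbers per representative are similar or the ICC is high. The missing professional status is an inconsistency with the stratified design and the knowledge models, with almost no measured cost in precision.

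**What to change.** Add professional status to the PEG, PR and AP models.

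Analyse each measure separately at person level, with a mixed model or GEE (with small-sample correction) clustered on the representative. Adjust for professional status and the person's own T0 status, and report standardised percentages by group and their difference.

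Define the main analysis on persons present at T0. Persons who join later have a starting status recorded only at inclusion, after randomisation, so handle them in a sensitivity analysis.

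If the representative-level model is kept, add professional status and use weights 1/[ICC + (1−ICC)/m] with m the number of persons at T0, plus robust standard errors. Do not weight crudely by number of persons, and do not use the T3 number: it is post-randomisation and is itself listed as an outcome.

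The cost is some wording and slightly more programming, since the documentation sheets already hold person-level data. The estimate becomes person-weighted rather than representative-weighted, which should be stated. Rare PEG needs a simpler fallback specified in advance.

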### Outcomes

The primary outcome measure is *knowledge*, which is operationalized as an understanding of decision-making processes in healthcare affairs and in setting realistic expectations regarding probabilities of benefits and harms of PEG, PR and AP to people with dementia.

Secondary outcome measures are: 1) legal representatives have obtained sufficient knowledge (using a cut-off of 70% correct answers in the knowledge test); 2) legal representatives have obtained sustainable knowledge, which is measured 6 months after intervention; 3) percentage of persons concerned affected by PEG, FEM or AP during follow up of 6 months; and 4) result of the first decision after intervention regarding PEG, PR and AP for the persons concerned including time to first decision.

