### Data collection

In the T0 baseline, data of legal representatives will be assessed according to age, gender, education status, activity status (professional or voluntary representative), time since appointment as legal representative and number of persons concerned. Additionally, baseline data and baseline outcome measurements of persons concerned will be assessed. For this, legal representatives will receive a pseudonymization list, documentation sheets and a standardized written introduction. A pseudonymization number will be assigned to each person concerned with dementia. All data will be given to the study site under this pseudonym. The legal representative, using data extracted from routine documentation, will fill in the documentation sheets. The age range, gender, diagnosis additional to dementia, presence of PEG, number and types of PR, name and dosage of antipsychotics will be assessed by multiple choice and free-response questions. Copies of the routine documentation (e.g., a list of drug prescriptions) will be passed on only if pseudonymization is safeguarded.

At T1, the primary outcome *knowledge* will be assessed (Table 1). To assess understanding and realistic expectations, a novel questionnaire was developed based on Bloom’s taxonomy [40], the *User Manual–Realistic Expectations* [41], the contents of the education program, and the evidence-based information for PEG, PR and AP in people with dementia. The questionnaire comprises 13 items: two items on the understanding of decision-making processes in healthcare affairs; two items on quality and validity of study results; and nine items on realistic expectations regarding probabilities of benefits and harms of PEG, PR and AP to people with dementia (with three items per intervention). All items are multiple choice questions with four choices, with only one correct answer. Questions with more than one answer and unanswered questions will count as a wrong answer. No summarizing score is given if four or more of the 13 questions remain unanswered.

**Table 1 Tab1:** Data collection

Outcomes	Measures	Follow-up
Knowledge	Questionnaire developed on the basis of evidence-based information and contents of the education program	T1, T3
First decision PEG	Standardised telephone interview	T2, T3
First decision PR	Standardised telephone interview	T2, T3
First decision AP	Standardised telephone interview	T2, T3
Physical restraints	Documentation sheet; medical and nursing records	T3

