Antipsychotics	Documentation sheet; medical and nursing records	T3
PEG	Documentation sheet; medical and nursing records	T3

T1 = at the end of / up to 2 weeks after the intervention; T2 = 3 month follow-up; T3 = 6 month follow-up

Legal representatives in the IG will receive the test at the end of the education program. They may complete the test immediately or return it by mail in the following 2 weeks. Participants in the CG will receive the test by mail at the same time.

At T2 (the 3-month follow-up), the results of the first decisions regarding PEG, PR and AP for the persons concerned will be assessed (Table 1). Decisions may have been initiated by legal representatives themselves (e.g., consultation for medication review), by relatives (e.g., worries about agitation) or by health professionals (e.g., required consent for PEG or PR). We define a decision as every consideration about PEG, PR or AP, regardless of the result.

Participants receive a documentation sheet for each intervention at the beginning of follow-up to assess the starting point of the decision-making process, presence of the intervention before and after the decision, reason or trigger for decision-making and changes regarding the intervention. The sheets may be used for personal documentation only or may be sent back to the study center.

Participants will be contacted by phone to ask if they had made a decision regarding PEG, PR and/or AP. If they had made a decision, they will either be reminded to fill out and return the documentation or directly interviewed by telephone to fill out the sheet. The first decision of each intervention will be recorded and classified in one of the four following categories, whereby 0 = no presence and 1 = presence of PEG, FEM and AP:

Category I: 0 ➔ 0 (No PEG / FEM / AP ➔ decision ➔ no PEG / FEM / AP).

Category II: 0 ➔ 1 (No PEG / FEM / AP ➔ decision ➔ new PEG / FEM / AP).

Category III: 1 ➔ 1 (PEG / FEM / AP ➔ decision ➔ still PEG / FEM / AP).

Category IV: 1 ➔ 0 (PEG / FEM / AP ➔ decision ➔ no longer PEG / FEM / AP).

The date of the decision will be documented.

At T3 (the 6-month follow-up), the sustainable knowledge of legal representatives will be assessed using the same test as at T1.

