Additionally, the number of PEG, PR and AP interventions in the persons concerned will be assessed (Table 1). The legal representatives will perform the assessment as at T0, filling out the documentation sheets and forwarding any copies of routine documentation. New diagnoses since baseline, the presence of PEG, the number and types of PR, medication data and decisions made about one of these interventions will be documented.

All persons concerned who are represented by one of the participating legal representatives at least for 2 weeks within the 6-month follow-up are eligible. If a person concerned who was assessed at T0 is no longer represented by the participant prior to end of follow-up, a documentation sheet will be filled out. The time of and reason for dropout, as well as the presence of PEG, number and types of PR and medication data at the time of dropout, will be documented. New persons concerned during the study period will be assessed at the time of inclusion and at T3. At the time of inclusion, a documentation sheet will be filled out, including time of inclusion, age range, gender, any diagnoses additional to dementia, the presence of PEG, number and types of PR and medication data.

Participants will receive the knowledge test and documentation sheets by mail or, if requested, by email. Participants in the CG have to submit the documents before subsequently beginning the education program (they may hand them over in person on the first training day).

Participants who had not made all three decisions regarding PEG, PR or AP for a person concerned at T2 will be additionally contacted by phone and asked again if they had made a decision since T2. Results of the first decision of each intervention will be recorded as in T2.

To reach a high compliance rate until T3, participants will receive stamped, addressed envelopes for returning outcome assessments by mail. Submission of all documents to the study center will be also possible by email or fax. If required, participants will be reminded by phone, and any of their questions about data assessment will be answered.

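### The first-decision analysis does not say whether PEG, PR and AP are tested separately or together, and its log rank test ignores the stratum used in randomisation

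*Protocol article*

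**What the plan says.** Four places in the protocol article describe this secondary outcome.

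- Outcomes defines it as the "result of the first decision after intervention regarding PEG, PR and AP for the persons concerned including time to first decision".
- Table 1 in Data collection has a row "First decision PEG" and matching rows for PR and AP. The text for T2 says "The first decision of each intervention will be recorded and classified in one of the four following categories".
- For T3, Data collection describes a second telephone contact for "Participants who had not made all three decisions regarding PEG, PR or AP for a person concerned at T2", and then: "Results of the first decision of each intervention will be recorded as in T2".
- Data analysis turns to "the results of the first decision about PEG, FEM or AP by the legal representative after T0". It describes a duration from T0 to the first decision, censored at 6 months or dropout, and says "Kaplan-Meier curves between both groups will be compared by the log rank test", provided the graphs show no clear departure from proportional hazards.

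The paragraph just before in Data analysis deals with "the percentage of these persons affected by PEG, FEM or AP (separately) per legal representative at T3". There the separation by intervention and the representative as unit are both explicit. FEM is read here as physical restraints (PR), as the context implies.

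Randomisation and blinding states that allocation is stratified into professionals and volunteers. The knowledge analyses at T1, and the model for T1 to T3, include professional status. The first-decision comparison does not mention it.

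**The concern.** Two things are left unsettled or badly fixed.

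**Unit.** The tested event could be a representative's first decision about one given intervention, or the first about any of the three. The references to persons concerned also allow a time for each person. These readings differ in event counts, in the number of tests and in whether clustering within a representative must be handled. If the unit stays open, it can be chosen after the data are seen.

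**Test.** A representative with more persons concerned has more occasions for a decision. Professionals and volunteers may differ widely in this, and so in time to first decision. Stratified blocks hold the professional share nearly equal in the two arms. An unstratified log rank test does not use that balance. It counts between-stratum variation that the design has removed, and it mixes fast and slow strata in one risk set, which dilutes the hazard ratio. Both effects cost power.

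**Working it through.** **1. The plan's own figure.** The only sizing is for knowledge at T1. A difference of 0.085 with SD 0.17 is 0.5 SD. The two-sided t-test at 5% then needs 86 per group (power 0.903). With 20% dropout, 86/0.8 = 107.5, so 108 per group and 216 overall. This reproduces. No event count, hazard ratio or power is stated for the first-decision outcome.

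**2. The wording side by side.**

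| Place | Per intervention? | Person or representative? |
|---|---|---|
| Outcomes | lists all three | refers to persons concerned |
| Table 1, T2 and T3 recording | yes | not stated |
| T3 re-contact rule | counts three decisions | a person concerned: each, or any one |
| Data analysis | not stated | legal representative |

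**3. Does the reading change the numbers?** Assume 172 representatives with m persons each, and independent 6-month decision probabilities p of 5%, 10% and 25% for PEG, PR and AP. With m = 3:

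- Per representative and intervention, 172 × [1 − (1 − p)³]: 25, 47 and 99 events.
- Per representative, any of the three: 172 × [1 − (0.95 × 0.90 × 0.75)³] = 172 × 0.736 = 127 events.
- Per person and intervention, 172 × 3 × p: 26, 52 and 129 events.

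Schoenfeld power at a hazard ratio of 1.5 is Φ(ln 1.5 × √(d/4) − 1.96), where d is the number of events. It gives 17%, 28% and 52% for the separate tests and 63% for the pooled one. For m from 1 to 5, pooled events run from 62 to 153, and separate events from 9 to 39 (PEG), 17 to 70 (PR) and 43 to 131 (AP). With m = 1 the person and representative readings coincide.

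**4. Which reading has more power depends on the effect.** Use the nursing-home prevalences in Background (5%, 12.5%, almost 30%) as decision probabilities, with 86 per arm and m = 5. The hazards −ln(1 − p) are 0.051, 0.134 and 0.357, sum 0.541. If only the PR rate doubles, the pooled hazard ratio is (0.541 + 0.134)/0.541 = 1.25, and power is 29% pooled against 94% separate. If only PEG doubles, it is 8% against 72%. If all three double, it is about 99% pooled against 72%, 94% and 99% separate.

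**5. Number of tests.** One pooled test has 5% error. Three independent unadjusted tests have 1 − 0.95³ = 14.3%.

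**6. Plain against stratified log rank.** Simulation for AP: 86 per arm, half professionals in each arm, one record per representative, exponential times with hazard m × 0.357 over 6 months, hazard ratio 1.5. With 1 person per volunteer and 8 per professional, the plain test had 19% power and 0.8% type I error. The stratified test had 57% and 5.5%. A second run of 5,000 trials per setting, varying the professional caseload, gave:

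| Persons: volunteer / professional | Power plain / stratified | Type I error plain / stratified |
|---|---|---|
| 1 / 1 | 34% / 34% | 5.4% / 5.4% |
| 1 / 2 | 42% / 45% | 4.6% / 5.1% |
| 1 / 3 | 41% / 50% | 3.6% / 5.1% |
| 1 / 5 | 34% / 55% | 2.1% / 5.4% |
| 1 / 8 | 19% / 58% | 0.6% / 4.6% |

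The Monte Carlo standard error near 5% is √(0.05 × 0.95/5000) = 0.3 percentage points, so the stratified values are compatible with 5%. The gap is smaller for the rarer interventions. At 1 / 8, power is 24% against 43% for PR (12.5%) and 19.2% against 24.5% for PEG (5%).

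**The case against.** The best reply is that one reading fits nearly all the text. Participants get a documentation sheet for each intervention, Table 1 has three rows, the recording rule is per intervention at both T2 and T3, and Data analysis names the legal representative. The list joined by *or* is shorthand elsewhere in the article too: the re-contact rule uses it while counting three decisions. On this view only a clarifying word is missing, in the last of four secondary outcomes. Most of this stands, and it is why the recommended unit is one record per representative per intervention.

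A reader might infer that the article defines three different endpoints. It does not. Pooling is only one reading of the analysis sentence, and the phrase about a person concerned may mean any one person. It also belongs to a re-contact rule, not to the analysis.

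A reader might also infer that the planned test inflates type I error by ignoring clustering. With a design effect of 1 + (m − 1) × ICC, a naive per-person test would have a true error between 5.2% (m = 3, ICC 0.01) and 14.4% (m = 5, ICC 0.20). That describes a person-level analysis, which Data analysis does not name.

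Finally, prevalence is not a decision rate, since the article counts every consideration of an intervention as a decision, and caseloads are not given. The figures therefore show direction and a possible range, nothing firmer.

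The reply does not touch the unstratified test. That is stated in the article, and it sits oddly beside the stratified randomisation and the adjusted knowledge analyses.

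**Conclusion.** The point holds in limited form. The analysis text leaves open whether PEG, PR and AP are tested separately or together, and the references to persons concerned leave some doubt about the unit. The recorded data point to one first decision per representative per intervention. Separately, the stated log rank test omits the randomisation stratum. If caseloads differ strongly between professionals and volunteers, it is conservative and loses power: 19% against 57% in the assumed 1 versus 8 case for AP, but only 42% against 45% at 1 versus 2, and nothing at equal caseloads.

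All these figures rest on assumed decision probabilities, caseloads, an equal split of professionals and volunteers, and a hazard ratio of 1.5. The article states no power, event count or family-wise error control for this outcome, so no stated figure is contradicted. The primary outcome and the sample size are unaffected.

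**What to change.** In Data analysis, state that time to first decision is analysed separately for PEG, PR and AP, with one record per legal representative for each intervention, and that each comparison uses a log rank test stratified by professional status. In Outcomes, name the representative's first decision about each intervention, for any person concerned. In the T3 re-contact rule, say that a representative is called again if a first decision is still missing for any of the three interventions.

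The cost is wording in three places. No new data are needed: the first decision per intervention, its date and professional status are already recorded, and stratifying the test is free. The downside is three secondary p-values instead of one, with up to 14.3% family-wise error if the tests are independent and unadjusted. Report them as secondary. A Cox model with variance clustered on the representative is needed only if a per-person analysis is chosen instead. This change leaves the time origin as written.
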